**Methods:**

A randomized, controlled clinical trial will be conducted. Older volunteers with PD will be randomly assigned to one of the two groups studied: (1) exercise or (2) AMPS + exercise. Both groups will undergo an exercise program of 24 sessions, for 12 weeks, performed twice a week. Before exercise sessions, the group AMPS + exercise will receive a session of active AMPS, while the group exercise will receive an AMPS sham intervention. Shapiro-Wilk’s and Levene’s tests will be used to check for data normality and homogeneity, respectively. In case parametric assumptions are fulfilled, per-protocol and intention-to-treat analyses will be performed using a mixed model analysis of variance to check for group*time interaction. Significance level will be set at 5%.

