#### Outcomes {12}

The results will be evaluated at 2 time points: (1) baseline (before starting the intervention program) and (2) after 12 weeks of intervention (after 48 h to 1 week from the last intervention). The primary outcomes will be (1) quality of life (PDQ-39), (2) heart rate variability (HRV) indices, and (3) VO2peak (cardiopulmonary exercise testing). Secondary outcomes include (1) 24-h blood pressure (3 channel Cardio Map digital equipment), (2) sleep quality (actigraph monitor), (3) VO2 at the anaerobic threshold (cardiopulmonary exercise testing), (4) dynamic balance (Tinetti Scale, TUG), and (5) gait velocity (10-m Walk Test).

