##### Heart rate variability

HRV is defined as the variation that occurs in the time interval between consecutive heartbeats and it has been proposed that its behavior depends on autonomic modulation, as well as its implications on cardiovascular mortality [31]. This time it will be done by continuous recording of RR intervals with 1000 Hz sampling frequency (Polar V800, Finland). R-R intervals will be recorded with a Polar V800 heart rate monitor (Polar, Oi, Finland); a sensor will be placed on the chest at the fifth intercostal space. Prior the beginning of data collection, volunteers will remain at rest for approximately 20 min for baseline heart rate and BP stabilization. Recording will occur under the following conditions: (1) resting in supine position for 15 min and (2) resting in orthostatic posture for 15 min. The volunteers will be instructed to maintain spontaneous breathing throughout the collection period in the supine and orthostatic postures. The participants’ respiratory rate will be recorded throughout the test. Heart rate variability will be analyzed through spectral analysis in an autoregressive model. The spectral components will be obtained at low frequency (LF, 0.04–0.15 Hz) and high frequency (HF, 0.15–0.4 Hz). The LF band is modulated by the sympathetic and parasympathetic autonomic nervous system (with sympathetic predominance), the HF band is associated with cardiac vagal control, and the LF/HF ratio is calculated to assess sympathovagal balance.

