### Statistical methods

#### Statistical methods for primary and secondary outcomes {20a}

The Shapiro-Wilk and Levene’s tests will be applied to check for data normality and the homogeneity of the variance, respectively. To check the interaction between the Groups (EX-G and AMPS-G) and time (baseline and post-intervention) a mixed ANOVA model with Bonferroni adjustment will be applied for the variables that meet the ANOVA assumptions. Otherwise, the data will be analyzed by the Wilcoxon (intragroup) and Mann-Whitney (intergroup) tests with a priori Bonferroni correction. For all tests, the significance level will be set at 5%.

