#### Methods in analysis to handle protocol non-adherence and any statistical methods to handle missing data {20c}

Per-protocol and intention-to-treat analysis will be performed. Per-protocol analysis will include only participants who attended at least 70% of the sessions and underwent baseline and final evaluations. Missing data will be addressed by a multiple imputation method.

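### Whether the trial tests group-by-time depends on a normality pre-test, and the rank-test fallback does not name a between-arm comparison of change

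*Protocol article*

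**What the plan says.** The Objectives section asks a comparative question: is exercise with AMPS more effective than exercise alone? Each outcome is measured twice, at baseline and after 12 weeks (Outcomes, item 12). HRV indices are one of three primary outcomes. They include a ratio of spectral powers: "the LF/HF ratio is calculated to assess sympathovagal balance".

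Statistical methods (item 20a) sets a two-stage rule.

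- **Pre-test:** "The Shapiro-Wilk and Levene’s tests will be applied to check for data normality and the homogeneity of the variance, respectively".
- **If the assumptions hold:** "To check the interaction between the Groups (EX-G and AMPS-G) and time (baseline and post-intervention) a mixed ANOVA model with Bonferroni adjustment will be applied".
- **If they do not:** "Otherwise, the data will be analyzed by the Wilcoxon (intragroup) and Mann-Whitney (intergroup) tests with a priori Bonferroni correction".

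The abstract makes the same link. Its "mixed model analysis of variance to check for group*time interaction" applies only if parametric assumptions are met. Neither place says what the pre-tests are applied to (raw values by cell, changes or residuals), which variable enters the Mann-Whitney test, or whether HRV indices are transformed.

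**The concern.** The treatment question is whether change differs between arms. Under this rule, a pre-test on the trial's own data decides whether that question is tested directly. If the pre-test fails, two kinds of test replace the interaction. The within-arm Wilcoxon tests address a different question: did each arm change? Significance in one arm and not in the other is not evidence that the arms differ. The Mann-Whitney test does compare arms, but the quantity compared is left open.

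This matters here because both arms exercise, and the abstract's Discussion expects both to improve. Separate within-arm tests will then often disagree by chance. A primary outcome could follow this route, and the choice between follow-up values and change would be made after the data are seen.

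**Working it through.** **Inputs.** From the protocol: two arms, two time points, 5% significance level, 19 per group needed and 25 enrolled, effect size 0.80 (Sample size, item 14). The effect size was set for systolic blood pressure and is used here only as a scale. Assumed, because the protocol gives no figures: baseline–follow-up correlation ρ of 0.5 to 0.7, two-sided tests, log-normal HRV, and a common exercise effect of 0.4 SD on the log scale. The plan has no figure of its own on this point to reproduce.

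**1. Within-arm tests when AMPS adds nothing.** If each arm's Wilcoxon test is significant with probability p, exactly one arm is significant with probability 2p(1 − p). The simulation (4,000 runs, log-SD 0.7, unadjusted 5%) gave:

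| n per arm | ρ | both significant | p = √both | 2p(1 − p) | simulated: exactly one | simulated: AMPS-G only |
|---|---|---|---|---|---|---|
| 19 | 0.5 | 0.110 | 0.33 | 0.44 | 0.444 | 0.212 |
| 19 | 0.7 | 0.255 | 0.50 | 0.50 | 0.500 | 0.251 |
| 25 | 0.5 | 0.170 | 0.41 | 0.48 | 0.492 | 0.246 |
| 25 | 0.7 | 0.393 | 0.63 | 0.47 | 0.462 | 0.246 |

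So the arms disagree in 44–50% of trials with no AMPS effect, and in 21–25% the disagreement favours AMPS-G. A Bonferroni division over four tests (an assumed family size) lowers the disagreement rate only to about 27% (n = 19) and 36% (n = 25).

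**2. What the Mann-Whitney test would do.** With no AMPS effect its rejection rate is 0.045–0.050 on follow-up values, 0.044–0.051 on raw change and 0.042–0.053 on log change. Each is a valid test of the arm difference. They differ in power.

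The interaction test in a two-by-two design is a t-test on change, with standardised effect d/√(2(1 − ρ)):

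- ρ = 0.5: 0.80/√1.0 = 0.80, giving 67% power at 19 per arm.
- ρ = 0.7: 0.80/√0.6 = 1.03, giving 87%.

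Power at d = 0.80 with 19 per arm:

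| Analysis | ρ = 0.5 | ρ = 0.7 |
|---|---|---|
| Mann-Whitney, follow-up values | about 64% | about 64% |
| Mann-Whitney, raw change (log-SD 0.7) | 35% | 51% |
| Mann-Whitney, log change | 62% | 84% |
| Planned interaction test, log scale | 67% | 87% |
| Baseline-adjusted model, log scale | 77% | 92% |

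**3. How likely is the fallback for HRV?** Shapiro-Wilk rejection rates at 5% for log-normal data, with skewness (e^{σ²} + 2)√(e^{σ²} − 1):

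| log-SD σ | skewness | single cell, n = 19 | single cell, n = 25 |
|---|---|---|---|
| 0.3 | 0.95 | 23% | 31% |
| 0.5 | 1.75 | 49% | 63% |
| 0.7 | 2.89 | 72% | 85% |
| 1.0 | 6.18 | 92% | 98% |

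At milder skewness (0.6) a single cell fails in only 12–15% of cases. If all four arm-by-time cells are tested and any failure triggers the fallback, the rates rise to 41–49% at skewness 0.6 and 65–72% at 0.95. Even exactly normal data would then fail in 1 − 0.95⁴ = 18.5% of trials (simulated 17–19%, treating the cells as independent).

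**The case against.** A reader might infer that the fallback contains no test of the treatment question at all. The text does not support that. It includes a between-arm Mann-Whitney test. On change scores this is a group-by-time test, and on follow-up values it is a valid, baseline-unadjusted comparison under randomisation. What stands is that the protocol does not say which it is.

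A reader might also take it as given that HRV is skewed. The protocol reports no mean, SD or distribution for any HRV index. Right skew is plausible for a ratio of two positive powers, but it remains an assumption. If skewness is mild, or if only residuals are tested, the fallback becomes less likely.

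The power gap should not be charged wholly to the fallback. At correlation 0.5 the planned interaction test itself has only 67% power, so the loss against it is about 3 points (67 − 64). The other 10 points up to 77% are the gain from baseline adjustment, which the protocol does not plan. At correlation 0.7 the loss against the planned test is 23 points (87 − 64).

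Nor does the protocol say that significance in AMPS-G alone would be read as superiority. The figures in step 1 show how often that pattern would arise, not how the authors would report it. The Bonferroni adjustment appears in both branches, so it is not peculiar to the fallback. How rank tests would be pooled after multiple imputation is detail that an analysis plan could supply, and it is no part of this point.

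An unseen analysis plan might also name the Mann-Whitney input. The rule itself, a pre-test that selects the analysis and sets within-arm tests beside a between-arm one, is fixed in the article.

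**Conclusion.** The point holds as a weakness of a stated rule and should be fixed. Which hypothesis is tested, and with what power, depends on a pre-test of the same data. The fallback combines within-arm tests that cannot answer the question with a between-arm test whose input is unnamed.

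With no AMPS effect and a common 0.4 SD improvement, the within-arm tests disagree in about 44–50% of trials. At 19 per arm and d = 0.80, Mann-Whitney on follow-up values has about 64% power, against 67–87% for the planned test and 77–92% with baseline adjustment. These figures rest on the assumed 0.4 SD change, correlation of 0.5–0.7 and log-normal outcome. The structural fault does not rest on them. Whether HRV reaches the fallback depends on a distribution the protocol does not give. At log-SD 0.5 or above, failure of a single cell is about an even chance or more.

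**What to change.** In Statistical methods (item 20a), and correspondingly in the abstract:

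1. Stop using the Shapiro-Wilk and Levene tests to select the analysis.
2. Prespecify one between-arm analysis for each continuous outcome, adjusted for its baseline value. Make the arm difference with its 95% CI the decisive result.
3. Analyse LF, HF and LF/HF on the log scale, and report ratios of geometric means.
4. If a rank method is kept, apply it to the between-arm contrast of change, or as rank ANCOVA, and label it a sensitivity analysis.
5. Report within-arm changes descriptively only.

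A smaller repair would be to name change as the Mann-Whitney input and make that comparison decisive. It would settle which hypothesis is tested but leave the pre-test in place.

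The cost is a rewording, since the baseline values are already collected. The one drawback is that HRV effects are reported as ratios rather than raw differences.

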#### Interim analyses {21b}

Not applicable. Interim analyses will not be performed in the present study.

#### Methods for additional analyses (e.g., subgroup analyses) {20b}

Not Applicable. Additional analyses are not planned in the present study.

#### Methods in analysis to handle protocol non-adherence and any statistical methods to handle missing data {20c}

Per-protocol and intention-to-treat analysis will be performed. Per-protocol analysis will include only participants who attended at least 70% of the sessions and underwent baseline and final evaluations. Missing data will be addressed by a multiple imputation method.

#### Plans to give access to the full protocol, participant level-data and statistical code {31c}

Participants may consult the information generated at any time during the execution of the project upon request to the investigator responsible for the study, who undertakes to provide cooperation and to propose ways to access it.

Likewise, the Responsible Researcher agrees with each participant to send the research report generated at the end of the study to the respective emails, as well as copies of the scientific articles that may result from the study.

### Oversight and monitoring

#### Composition of the coordinating centre and trial steering committee {5d}

This study is proposed by the leading researcher [name], coordinator of the Laboratory of Research in Clinical Kinesiology at the Catholic University of Maule. The trial will be directed by the researchers [name] and [name]. This trial was approved by the scientific ethics committee of the Catholic University of Maule and a does not require the supervision of a steering committee, since there are no invasive procedures, and the assessments and interventions are considered of low risk. Even though, all researchers will meet every 2 weeks to discuss the research progress and possible unforeseen events. Also, all intervention sessions will be supervised by at least two professionals experts in the field of rehabilitation/exercise intervention.

#### Composition of the data monitoring committee, its role and reporting structure {21a}

The protocol excludes vulnerable people and people with diseases that may hinder the application of the protocol. So, it can be considered of low risk and of short duration, thus not requiring an additional committee [40].

The leading researchers ([name] and [name]) will meet every 2 weeks with all researchers involved in this study to monitor the data, discuss the research progress and any adverse event that arises during the procedures. Researchers are instructed to report any issue to the leading investigators immediately.

#### Adverse event reporting and harms {22}

In the end of each intervention session, participants will be asked to report any complaints and symptoms produced by the proposed activity. Outcome assessor and the lead researcher will be in charge to collect and record this information throughout the study. Adverse events, undesirable effects, and incidents will be classified by specialists as treatment-related or non-treatment-related within 24 h of occurrence [41]. Common undesirable effects may include fatigue, dyspnea, and muscle soreness not lasting more than 24–48 h as a result of the exercise and AMPS intervention. In case these symptoms persist, or other related-treatment event occur, the participants will be asked to discontinue from this study and this will be immediately informed to the ethics committee who will decide whether the protocol should be suspended. All complications and dropouts will be reported in the final manuscript.

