## Introduction

### Background and rationale {6a}

Parkinson’s disease (PD) is a degenerative neurological disorder characterized by a loss of dopaminergic neurons at the substantia nigra level, leading to muscle tremor, rigidity, progressive bradykinesia, and postural instability, with great impact on the quality of life [1]. Based on international data, it can be estimated that there are more than seven million patients with PD worldwide [2]. Moreover, about 1 to 2% of the population over 65 years of age suffers from PD, rising to 3 to 5% in those over 85 years of age [3].

Gait disorders are one of the main therapeutic challenges in PD [4], involving a risk of fall, disability, and physical decline [5]. The progressive deterioration of the physical condition leads to a reduction in aerobic functional capacity and autonomy, thus affecting the ability to perform everyday tasks effectively [6, 7]. Indeed, it is estimated that between 40 and 70% of people with PD have falls, in which muscle weakness at lower limbs appears to play a key role, significantly reducing their postural stability [8]. These data allow us to consider elderly people with PD in a high degree of frailty, thus with high probability of suffering health problems due to the massive deterioration of physiological systems [9, 10].

In terms of intrinsic exercise capacity, studies have shown that the maximum oxygen uptake (VO_2_) of PD patients was no different from that of controls, but they reached their maximum VO_2_ earlier, suggesting a lower mechanical efficiency of movement during exercise, perhaps due to their muscle stiffness [11]. Moreover, some authors have studied the relationship between aerobic functional capacity and gait [12, 13]. Results showed a positive correlation between VO_2peak_ and gait speed, meaning that the lower the cardiorespiratory capacity the lower the gait speed.

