#### Plans to promote participant retention and complete follow-up {18b}

A weekly phone call will be made to participants in both groups, asking about their health status and reinforcing the pre-session recommendations for physical exercise. Moreover, the participants who wish and agree, will be added to a telephone messenger group app with the objective of solving doubts and share information and experiences about PD.

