#### Frequency and plans for auditing trial conduct {23}

The trial conduct will be continuously monitored by the principal investigators ([name] and [name]) and it will be discussed in the periodic meetings occurring every 2 weeks with all researchers involved. This trial was approved by the scientific ethics committee of the Catholic University of Maule and since the interventions (i.e. assessments and treatment) are considered of low risk, the supervision by an independent data monitoring committee was not required or considered for this study. However, as aforementioned, the researchers are committed to report any adverse events occurring during the study to the Ethics committee.

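### The scheduled harms question asks only for symptoms the participant links to the session, and no other contact is tied to adverse event recording, so capture of between-session events such as falls is not assured

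*Protocol article*

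**What the plan says.** The protocol article deals with harms in four places.

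- **Adverse event reporting and harms {22}.** At the end of each session, participants are asked to "report any complaints and symptoms produced by the proposed activity". The outcome assessor and the lead researcher record this information over the course of the study. Events, undesirable effects and incidents "will be classified by specialists as treatment-related or non-treatment-related within 24 h of occurrence". The section ends by promising that all complications and dropouts will appear in the final paper.
- **Plans to promote participant retention {18b}.** "A weekly phone call will be made to participants in both groups, asking about their health status". The call also repeats the pre-session advice. Its findings are not linked to adverse event recording.
- **Data monitoring committee {21a}.** All researchers meet every two weeks and discuss adverse events that arise in the course of the procedures. Researchers are told to pass any issue to the leading investigators at once.
- **Auditing {23}.** "the researchers are committed to report any adverse events occurring during the study to the Ethics committee".

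On falls, the background {6a} says "it is estimated that between 40 and 70% of people with PD have falls" and gives no period. Falls are not named in {22}, which lists fatigue, dyspnoea and muscle soreness as the common effects.

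**The concern.** A question limited to what the activity produced puts the causality decision with the participant. A fall at home that the participant does not connect with the last session lies outside what was asked. The specialists can classify as unrelated only those events that reach them, so the one scheduled question is poorly suited to supplying that class.

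This matters because the direction of any effect on falls is open. The exercise programme includes walking on ramps {11a}, Hoehn and Yahr stages 1 to 3 are eligible {10}, and the Discussion credits AMPS with effects on walking and balance. The filter may also work unevenly between arms. Active AMPS is set at pain threshold and sham at the threshold of touch {11a}, so participants on active treatment may have more reason to attribute a symptom to the session. A comparison of harms by arm would then partly reflect attribution.

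**Working it through.** There is no design figure to reproduce. The check is to compare the scope of each step, and then to set the contact schedule against the 24 h limit.

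**Scope, side by side**

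| Step | Section | Events covered | Limited by attribution? |
|---|---|---|---|
| Scheduled question | {22} | Complaints and symptoms from the activity, asked at session end | Yes, by the participant |
| Classification | {22} | Related and unrelated events | No |
| Weekly call | {18b} | Health status, both groups | No, but no stated link to event recording |
| Two-weekly review | {21a} | Adverse events arising in the procedures | In effect, by setting |
| Notice to ethics committee | {22} | Persisting symptoms or other related events | Yes |
| Notice to ethics committee | {23} | Any adverse event in the study | No |
| Final paper | {22} | All complications | No |

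The scheduled question is among the narrowest steps, while classification, the {23} commitment and publication are among the widest. The one routine contact that asks without attribution, the weekly call, is not connected to them. {23} presents its wide commitment as something already described, but no earlier section sets out collection that wide. The two statements on what goes to the ethics committee also differ.

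**The 24 h limit and the contact schedule**

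Inputs: exercise twice a week; an AMPS or sham session 24 h before each exercise session {11a}, both at the facilities {18a}; one call a week {18b}. Session length is ignored.

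- Scheduled contacts per week: 2 exercise + 2 AMPS or sham + 1 call = 5.
- Hours in a week: 7 × 24 = 168.
- Time between each AMPS session and its exercise session: 2 × 24 = 48 h.
- Remaining time, in two gaps: 168 − 48 = 120 h.
- Without the call, the longer gap is at least 120 / 2 = 60 h.
- With the call placed as well as possible inside one of these gaps, there are three gaps and the longest is at least 120 / 3 = 40 h.

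Every week therefore has at least one stretch of about 40 h with no scheduled contact. An event early in that stretch is first heard of after the 24 h from occurrence have passed, unless the participant gets in touch unprompted. The text does not say how the limit applies then.

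**Falls**

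The 40–70% in {6a} has no period and describes people with PD in general. It shows that falls are a foreseeable event. It does not give a rate for 12 weeks in this sample.

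**The case against.** The strongest reply is that the protocol has other routes. The weekly call carries no attribution. {22} expressly provides for unrelated events and incidents and for recording over the course of the study. {23} covers any adverse event, and {21a} has researchers raise any issue at once. Participants are seen about four times a week, so dizziness on the day after an AMPS session would fall on an exercise day with at least two professionals present. The harms sentence may also paraphrase a form that is not shown, and no between-arm comparison of falls is planned.

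Much of this stands, and it rules out several stronger readings that a reader might infer:

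- **That falls and other between-session events will go uncounted, or that the promise to report all complications cannot be met.** The routes above may well bring such events to light. The text only fails to assure it.
- **That a given number of the 50 participants will fall, or have a fall missed, in 12 weeks.** This needs a period for the 40–70% that the document does not give, and it would apply a general PD figure to a screened sample.
- **That the low-risk statement contradicts the background.** {6a} lets the authors "consider elderly people with PD in a high degree of frailty, thus with high probability of suffering health problems", while {21a} says "The protocol excludes vulnerable people and people with diseases that may hinder the application of the protocol". The first describes the general population and the second those left after the exclusions, so both can be true.

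The reply does not remove the core. The article does state a collection rule, and that rule limits reports by the participant's own attribution. The other routes are not said to feed the adverse event record. Uneven attribution between arms remains a possibility and is not shown; participant blinding may reduce it.

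**Conclusion.** The point holds as one of fit between sections. The scheduled harms question is narrower than the classification and reporting it is meant to feed, and the contact that could fill the gap is not tied to event recording. Capture of falls and other between-session events is therefore not assured.

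Its size in events cannot be stated from the document. What can be stated is that five scheduled contacts a week still leave a gap of at least about 40 h against a 24 h classification limit. This assumes a regular weekly pattern and exactly one call a week. The judgement also assumes that the case report form follows the wording in {22}. If the form already asks an open question and takes in events from the call, only the text needs correcting. The change is worth making because falls not recorded during follow-up cannot be reliably recovered later.

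**What to change.** 1. In {22}, replace the question with an open one: any health problem, injury or fall since the last contact, whatever the participant thinks caused it.
2. In {18b} and {22}, state that events reported on the existing weekly call, including falls, are recorded as adverse events in both arms.
3. Leave relatedness wholly to the classifying specialists.
4. Report all events by randomised arm.
5. Reconcile {18b}, {21a}, {22} and {23} on which events are recorded, reviewed and sent to the ethics committee, and state how the 24 h limit applies to events first heard of later.

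The cost is a reworded question, a line on the call form and some text. The downside is small: more unrelated events to record and classify. No treatment, visit or outcome changes.
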